#### Monitoring intensity and progression

The 10-point Rating of Perceived Exertion (RPE) scale will be used to monitor exercise intensity during each exercise session [118]. Participants will be instructed to exercise at a level of 3–6 on the 10-point RPE scale (12–16 on the 15-point scale). This corresponds to the target HR range detailed above and is a suitable alternative to regular HR monitoring [119]. In addition, HR monitors (Polar, NY, USA) will be used at 3-week intervals throughout the intervention to ensure that the intensity of aerobic exercise being performed aligns with the absolute workload prescribed and to monitor individual exercise progression. If a participant’s HR is outside of his target HR range, exercise intensity will be modified to ensure training within the target HR zone. Participants who need to increase their aerobic exercise workload will first increase exercise duration (e.g. walking minutes), followed by the intensity of exercise (e.g., walking speed). If a participant is able to perform ≥12 repetitions and 3 sets of any given resistance training exercise, the resistance level used for that exercise will be increased (e.g., from a medium to a heavy band). Participants in the group-supervised arm of the intervention will wear a HR monitor during group exercise classes as indicated. Participants in the home-based arm of the intervention will be given a HR monitor to use for the duration of the intervention and will be taught how to use and read their HR response, wearing the monitor as instructed by their health coach.

#### Group-supervised program

Participants in the group-supervised program will take part in classes led by a CEP/RKin 3 times per week for a period of 6 months. At each site, groups will commence as soon as 2 men have been randomized to a group and will grow to include 4–8 participants to ensure adequate supervision and progression. Participants will be provided with a set of resistance bands to support additional independent exercise.

#### Home-based program

Participants in this arm will receive equipment (exercise bands, ball, mat, heart rate monitor) free of charge to support home exercise. The frequency, intensity, time, and type of exercise are the same as in the group-supervised program although specific exercises in the aerobic component may be modified to incorporate participant preference and interest.

Since the strongest evidence in terms of exercise delivery appears to support supervised programs [78, 100], we have incorporated enhancements to prior home-based programs [66, 69, 72] based on emerging data in the field of behavioural interventions [120–122] as well as data from our phase II trial [101]. In particular, we will employ cutting-edge smartphone technology and the use of Fitbits as well as remote ‘health coaches’ to provide support to patients during the intervention phase and ideally optimize participation and adherence.

#### Health coaching

A growing body of research supports the effectiveness of the role a ‘health coach’ in chronic disease management [121, 123]. A health coach is a clinic-based health promoter trained to specifically stimulate and support initiation of and adherence to health behaviours (e.g., exercise, improved nutrition). Participants in the home-based arm of the intervention will work with a remote health coach, following a protocol adapted from Spring et al.’s successful trials in improving physical activity and weight loss [120, 121, 124, 125] as well as our prior experience in the phase II trial [101] and other trials by members of our group [126–129] (Additional file 3: Table S2). The health coach will meet with each home-based participant at study entry to help set goals and will make contact with participants every week to review uploaded exercise data in relation to goals. In addition to weekly contacts made via phone or electronic device, health coaches will meet face to face with participants once a month during the intervention period. This will support the development of alliance between participant and health coach and will include items that may not be possible in phone or electronic-based contact.

To enhance health coach-participant interactions, we will use specialized health promotion software for smartphones (an ‘app’) from NexJ Systems, Inc. (Toronto, Canada). Home-based study participants will receive smartphones, loaded with health monitoring and communication software and a wearable activity tracker (Fitbit) to use for the duration of the intervention. NexJ software effectively interfaces with Fitbit activity trackers to capture all of the features that the Fitbit tracks. Previous research demonstrates that Fitbit results are reliable, valid measurements of exercise adherence [130, 131]. These data will allow health coaches to better support participants, providing them with tools and suggestions for maintaining or increasing adherence based on Fitbit results.

#### Tapering

Tapering is designed to enable participants to achieve weekly exercise goals in an increasingly independent manner. Ultimately this will prepare participants to continue with regular exercise following the active intervention. To aid with this transition to independent exercise in the group arm, the number of weekly supervised exercise sessions offered to participants will be reduced from 3 to 2 in the fifth month and to 1 in the final month of the intervention. Participants will be asked to increase the number of independent exercise sessions to maintain a total of 4 to 5 sessions of exercise per week. In the home-based program, the frequency of contact with health coaches will be reduced from every week to every 2 weeks in months five and six and text message support will be reduced to 24-h turnaround time.

### Outcomes and measures

#### Co-primary outcomes

Our co-primary outcomes are fatigue, as measured by the Functional Assessment of Cancer Therapy–Fatigue (FACT-F) [132], and functional endurance, assessed with the 6-min walk test (6MWT). The FACT-F includes 13 items measuring cancer-related fatigue. It has excellent reliability and validity and published normative data [133]. Fatigue is a common symptom in men on ADT and fatigue in cancer patients is negatively correlated with many components of QOL [134–136]. It has been shown to improve consistently with exercise in prior trials in men on ADT [78, 79, 100]. The 6MWT is a commonly used, validated measure that assesses functional endurance [137, 138]. Physical fitness commonly declines with ADT use and improves with exercise [30, 68–70, 72, 73].

#### Secondary outcomes

##### Quality of life – General

General QOL will be assessed using the Functional Assessment of Cancer Therapy – General (FACT-G). It is a well-validated and widely used QOL measure that has been an outcome in major PC exercise trials [80, 139]. It can be completed in 8–10 min and has published normative data [140, 141].

##### Quality of life – Prostate-specific

Prostate-specific QOL will be assessed using the Functional Assessment of Cancer Therapy – Prostate (FACT-P) [142] which supplements the FACT-G with 12 prostate-specific items covering domains of urinary function, sexual function, pain, and related symptoms. It is also well-validated and has been used in multiple prior exercise trials [80, 142].

##### Physical fitness

Prior to the start of fitness testing, resting HR, BP, and oxygen saturation will be measured. Musculoskeletal fitness will be assessed using the 5-times sit-to-stand test, a common, simple, and validated measure of functional lower body performance and strength [143–145]. In addition to this, grip strength will be assessed as a measure of upper body strength [146] using a Jamar dynamometer and recording the highest of three readings for each hand. This measure is responsive to ADT use [12], and predicts long-term disability and mortality in middle-aged and older adults [147].

##### Body composition

Body fat percentage, fat-free mass, and fat mass will be measured using bioelectrical impedance analysis (BIA) with the Tanita TBF-300A device (Illinois, USA). Additional anthropometric measurements include waist circumference (WC), WC:hip ratio, and body mass index, following the standardized CSEP-PATH protocol [148]. In addition, BMD will be measured at lumbar spine, total hip, and femoral neck using dual x-ray absorptiometry (DXA).

##### Biological outcomes

Blood will be collected at three time points (baseline, 6 months, and 12 months) to analyze fasting blood glucose, lipid profile (total cholesterol, low density lipoprotein, high density lipoprotein, triglycerides), hemoglobin, glycosylated hemoglobin (HbA1c), total testosterone, as well as prostate-specific antigen (PSA) levels. These outcomes are being measured given the impact of ADT and exercise on various biological endpoints. More specifically, ADT leads to deleterious effects on blood glucose and cholesterol levels, whereas exercise may be associated with their improvement. Hemoglobin levels will be assessed since ADT leads to mild declines in hemoglobin that may affect fatigue, QOL, physical fitness, and adherence [70, 149, 150]. Glycosylated hemoglobin will be collected since regular exercise has been shown to reduce HbA1c levels whereas ADT is associated with worse insulin resistance and diabetic control [13, 52, 151]. Total testosterone levels will be collected to confirm that participants who are not actively on ADT during the intervention period are in an androgen-deprived state for the duration of the intervention. PSA is a standard safety measure, since there is theoretical evidence that exercise leads to an acute increase in testosterone that could aggravate PC [152]. In multiple prior exercise studies in men on ADT, PSA has been found to be unaffected following bouts of training or over the course of an intervention [30, 70, 73].

##### Costing and utility outcomes

To allow cost-effectiveness analysis, both the EQ-5D-5 L and a patient costs diary will be used. The EQ-5D-5 L is a well-validated, widely used, generic, off-the-shelf preference instrument that measures patient utilities across 5 dimensions of health (mobility, self-care, usual activities, pain/discomfort, and anxiety/depression) [153, 154]. It was originally known as the EuroQol, and has been widely used throughout the world in both clinical investigations and health policy determinations [155]. A total of 3125 unique combinations of scores across the 5 levels of each of 5 dimensions can be generated, each of which can be converted into a utility score based on population-weighted responses from either a United Kingdom-based population cohort or a United States-based cohort [154]. It can be completed in 5 min.

Resource utilization, out-of-pocket costs, and productivity costs will be estimated using a patient cost diary that we have used in prior PC studies, adapted for this study based on patient feedback and response analysis in the phase II trial. More specifically, the patient cost diary will capture: i) hospitalizations/medical events; ii) physician/other health professional services including hospitalizations and outpatient diagnostic tests; iii) drugs, including drug costs unrelated to ADT; iv) equipment costs; v) community services and home care; vi) productivity costs; vii) exercise-specific costs; and viii) out-of-pocket costs.

##### Adherence

Program adherence and predictors of adherence will also be assessed. We recognize there is no perfect, all-inclusive definition of adherence. We will therefore measure different elements of adherence in this trial. Our primary adherence measure is the proportion of individuals in each arm who achieve at least 150 min of MVPA at both the three-month and six-month time points based on objective measurements via accelerometry. A target of 150 min is recommended by both Cancer Care Ontario’s guideline for cancer survivors [117] and the revised Canadian Society for Exercise Physiology (CSEP) guideline for adults and older adults [156]. Recognizing limitations of accelerometry (e.g. technical malfunction, incomplete wearing, not capturing all activities) we will also capture self-reported MVPA with the Godin Leisure Time Exercise Questionnaire (GLTEQ) at each time point. The GLTEQ is a brief, self-administered validated questionnaire that records light, moderate, and vigorous exercise performed each week in 15-min increments [157, 158]. For those in the group supervised arm, we will capture weekly attendance at exercise sessions. For those in the home-based program, we will measure three elements of adherence/engagement: a) Fitbit step counts; b) frequency of health coach contacts; c) frequency of use of the smartphone app.

Study participants will be asked to wear Actigraph GT3X (Pensacola, FL) accelerometers daily from awakening to bedtime for 1 week at each assessment time point (including baseline). Accelerometers are reliable [159] and non-obtrusive, and capture all physical activity during waking hours, thereby providing information on total physical activity during the time period of observation [160]. Accelerometer data will be extracted in 60-s epochs and screened using standard methods for: (i) at least 4 days of valid data, including (ii) at least 10 h of wear time per day; (iii) continuous non-wear time (periods of time with zero movement counts per minute) of more than 1 h. Total time spent in MVPA (> 1952 movement counts per minute [161]) will be calculated for the week. Additionally, accelerometer data enables the capture of sedentary behaviour using a protocol of time spent in activities with < 100 counts per minute and time spent inclined (using the inclinometer setting).

Predictors of adherence were selected based on a social ecological framework (Fig. 2). Potential determinants of exercise adherence and the relationship between these determinants will be examined using validated measures at each level: exosystem, mesosystem, and microsystem. Exosystem will be examined via participant postal codes, which will be collected to map where participants live in order to obtain information about neighbourhood resources and environment. This will provide details about the walkability and access to recreation in participant neighbourhoods [162]. Mesosystem variables include assessment of autonomy support and social relatedness. We will use the Health Care Climate Questionnaire (HCCQ short form) [163], a 6-item self-report measure that assesses patients’ perceptions of the degree to which their health care ‘network’ is autonomy supportive. The modified HCCQ, which allows the assessment of provision of autonomy support from appropriate: (1) group members; (2) exercise instructors, and (3) health check ‘system’ [164] (i.e. 3 scales) will be used. Relatedness to Other Exercisers will be used as a social connectedness indicator of adherence using the Psychological Need Support and Frustration Scale – Relatedness Items [165]. This is an 8-item scale with good psychometric properties that assesses how individuals feel connected to other exercisers. The microsystem includes a measure of motivation, which will be assessed using the Behavioral Regulations in Exercise Questionnaire-2 (BREQ-2) [166, 167]. A modified version of this questionnaire that does not include the amotivation scale (4 items) will be used since participants who have consented to an exercise trial are likely not to be amotivated. The BREQ-2 is a 15-item inventory assessing extrinsic, introjected, identified, and intrinsic regulations. Planning, Attitudes, & Barriers will be assessed using a scale validated for cancer patients [168, 169].

**Fig. 2 Fig2:**
[figure not shown]
Social Ecological Framework for Understanding Exercise Determinants

##### Sedentary behaviour

An exploratory outcome will be change in sedentary behaviour, which is defined as **any waking activity characterized by an energy expenditure ≤ 1.5 metabolic equivalents**
*and*
**a sitting or reclining posture.** There are currently no data on men on ADT on levels of sedentary behaviour. These data will be obtained from accelerometry at the assessment time points.

### Safety

The CEP/RKin will review exercise precautions and safety during the intervention orientation. In addition, participants are encouraged to review the manual prior to commencing independent exercise sessions. All exercise personnel are trained in cardiopulmonary resuscitation (CPR) and automated external defibrillator (AED) use and have received safety training at each site. Possible adverse events during intervention and post-intervention phases will be captured using the National Cancer Institute Common Terminology Criteria for Adverse Events (CTCAE) v4.0. There is no independent data monitoring committee given the lack of anticipated safety concerns based on multiple prior trials of both interventions.

### Sample size calculation

A total of 200 participants (100 per arm) gives an estimated 81% power for analysis of the FACT-F and 6MWT for non-inferiority and will also provide accurate estimates of parameters related to secondary outcomes. Details are shown in Additional file 4: Methods. There are no planned interim analyses or early stopping rules.

### Statistical analysis

#### Co-primary outcomes

The primary analysis will use a Bayesian analysis of covariance (ANCOVA) model to regress the change in FACT-F and 6MWT values between baseline and 6 months against the baseline value, the treatment group variable and variables representing stratification by centre and length-of-ADT. We will treat the high-intensity group (group supervised; higher level of supervision and greater resources) as the reference.

For each primary outcome, we will compute the Bayesian posterior probability that the low intensity group is non-inferior to the high intensity group (i.e., that the mean difference between groups is larger than the non-inferiority margin -**δ**). If either of these probabilities is large enough (i.e. > 97.5%) then we will declare the home-based group to be non-inferior for that outcome. One advantage of a Bayesian approach is that it allows us to assign posterior probabilities to the 4 possible outcomes of the study (illustrated in Fig. 3): (1) Home-based inferior only for 6MWT; (2) Home-based inferior only for FACT-F; (3) Home-based inferior for both outcomes; and (4) both non-inferior. Another advantage is that it allows a more useful presentation of individual results than a simple confidence interval or *p*-value: for example, we will be able to say that the mean difference lies below –**δ** (i.e., home-based is inferior) with probability X%, that it lies between –**δ** and 0 (i.e., home-based is worse but non-inferior) with probability Y% and that it is above 0 (i.e., home-based is better) with probability Z%. Finally, the outputs of the Bayesian model can be used as probabilistic inputs for the economic analysis. The Bayesian analyses will use non-informative priors, allowing the results to be data-driven and make direct probability statements about non-inferiority.

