### Baseline assessment

The baseline assessment consists of obtaining socio-demographic and clinical data as well as assessing fitness using measures of resting heart rate (HR), blood pressure (BP), oxygen saturation, body composition, upper and lower body strength testing, and a measure of functional endurance. Participants will also complete a series of questionnaires (to assess QOL, fatigue, and exercise adherence, including prior exercise program participation [114]) and will be scheduled to complete both a BMD test (if one has not been completed within the past year as per standard of care) and blood work. All measures are detailed below and summarized in Table 1. First aid and emergency equipment and supplies will be on hand for all testing and training sessions.

**Table 1 Tab1:** Summary of Study Measures at Specified Time Points

Domain/Measure	Time required	T_0_: (Baseline)	T_1_: (3 mo.)	T_2_:6 mo. (End Int.)	T_3_: 9 mo. (3 mo. f/u)	T_4_:12 mo. (6 mo. f/u)
Quality of life						
FACT-P	4–5 min	●	●	●	●	●
FACT-G	8–10 min	●	●	●	●	●
FACT-F (co-primary)	5 min	●	●	●	●	●
Physical Fitness						
6MWT (co-primary)	6 min	●	●	●	●	●
Sit-to-Stand Test	1 min	●	●	●	●	●
Grip Strength	1 min	●	●	●	●	●
Biological Outcomes^a^	< 5 min	●		●		●
Blood glucose						
Cholesterol profile						
PSA (safety)						
Testosterone^c^						
Haemoglobin (covariate)						
HbA1c (covariate)						
Body Composition						
Bone mineral density	30 min^b^	●				●
Body composition^d^	5 min	●		●		●
Adherence						
Accelerometer	–	●	●	●	●	●
GLTEQ	< 5 min	●	●	●	●	●
Sessional attendance^e^	–					
Adherence Predictor Variables						
HCCQ	5 min	●				
BREQ2	5 min	●		●		●
PNSF	5 min	●		●		●
PAB	5 min	●		●		●
Sedentary Behaviours	5 min	●		●		●
Cost-Effectiveness						
Health questionnaire	5 min	●	●	●	●	●
EQ-5D	5 min	●	●	●	●	●
Study Completion	5 min					●

^a^ All biological measures are considered to be standard of care at baseline and 12 months. PSA is considered to be standard of care at all 3 time points. Blood glucose, cholesterol profile, and haemoglobin tests at 6 months are NOT standard of care

^b^ Can be done on separate day to reduce participant burden

^c^ Will only be measured in participants who are not on continuous ADT for the duration of the intervention

^d^ Includes BIA, waist circumference, and waist circumference: height ratio

^e^ Only for those in supervised groups (done weekly)

*Abbreviations***:**

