**Fig. 3 Fig3:**
[figure not shown]
Illustration of Four Possible Scenarios in Non-Inferiority Testing for Proposed 2-Arm Trial. We will compare groups by means of ANCOVA using the baseline score as the covariate. After fitting a Bayesian model to each outcome, we will evaluate the probability in each of the 4 regions in the figure above. We can calculate the probability that: 1. Both the 6MWT and FACT-F fatigue scores are non-inferior in the home-based arm. This is the green region (**b**). 2. Both the 6MWT and FACT-F fatigue scores are inferior in the home-based arm. This is the grey region (**c**). 3. The 6MWT score is non-inferior in the home-based arm. This is the green region (**b**) plus the blue region (**a**). 4. The FACT-F Fatigue score is non-inferior in the home-based arm. This is the green region (**b**) plus the gold region (**d**). If either probability in (3) or (4) is above 97.5%, then we will declare non-inferiority of the home-based intervention.

Since this is a non-inferiority trial, the primary analysis will be per protocol, which in the presence of non-adherence to exercise is more conservative than intention-to-treat (i.e., less likely to conclude groups are similar when they are not). Two secondary analyses of the primary outcomes will be conducted. First, we will make the above between-group comparison of the changes in FACT-F and 6MWT scores from baseline to each follow-up time point. Secondly, we will perform an intention-to-treat analysis, including outcomes on subjects who were non-adherent to their exercise program. We will also conduct within-group analyses of change over time for the co-primary outcomes to understand the effects of each exercise modality on these outcomes and to facilitate comparisons with published studies.

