#### Secondary outcomes

Analyses for each of our secondary outcomes (QOL, fitness, biological, and body composition) will use mixed effects models for data at all time points incorporating within-person correlation. Within-person correlation of residuals will be handled by an autoregressive (AR1) error structure and factors will also be added for the 2 stratification variables (centre, ADT duration). All of these secondary outcomes will be analyzed as continuous variables after examining distributions to ensure symmetrical (approximately normal) distributions. Skewed data will be transformed as appropriate.

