#### Adherence

Several analyses will be used to assess adherence to the exercise programs and the relationship of adherence to both time and potential predictors. Adherence will be defined as a binary variable for the primary analysis, which uses accelerometry to measure MVPA. We will assess adherence over 4 distinct periods: 0–3 months, 3–6 months, 6–9 months and 9–12 months, so that each subject has up to 4 observation periods for adherence-based analyses. Our first analysis of adherence will simply be the calculation of percentages adhering in each group in each of the 4 time windows. Chi-squared or Fisher’s exact tests will compare adherence across groups within each of the time windows. All further analyses will be done on the sequence of 4 adherence measures on each subject using a generalized estimating equation (GEE) logistic regression model with an AR1 correlation structure.

Predictors of adherence will be examined at the exosystem, mesosystem, and microsystem levels using specific questionnaires as detailed earlier. These will be considered for inclusion in models examining each of the adherence variables separately. Mediation/moderation analyses will be explored based on the primary findings.

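### Haemoglobin is labelled a covariate but no described model adjusts for it; adding its baseline value to the co-primary ANCOVAs is a small, nearly free improvement (minor)

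*Protocol article*

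**What the plan says.** In the protocol article, Table 1 (Baseline assessment) attaches a role to some of the blood tests. PSA is marked as a safety measure, and two tests are marked as covariates: "Haemoglobin (covariate" and "HbA1c (covariate". Both are drawn at baseline, 6 and 12 months. The table's footnote treats all biological measures as standard of care at baseline and 12 months; the 6-month haemoglobin test is not.

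The Biological outcomes section gives the reason for measuring haemoglobin: "ADT leads to mild declines in hemoglobin that may affect fatigue, QOL, physical fitness, and adherence".

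The described models are these:

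- Co-primary ANCOVA (Statistical analysis, Co-primary outcomes): change from baseline to 6 months is regressed "against the baseline value, the treatment group variable and variables representing stratification by centre and length-of-ADT".
- Fig. 3 caption: "We will compare groups by means of ANCOVA using the baseline score as the covariate".
- Mixed models (Statistical analysis, Secondary outcomes): "factors will also be added for the 2 stratification variables (centre, ADT duration". The post-intervention models are described as similar.
- Adherence models: "Predictors of adherence will be examined at the exosystem, mesosystem, and microsystem levels using specific questionnaires as detailed earlier".

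The text after the Fig. 3 caption makes the per-protocol analysis primary. Outcomes of non-adherent men enter through a secondary intention-to-treat analysis.

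**The concern.** The article names a variable as a covariate and ties it to both co-primary domains, fatigue and fitness. It then lists the terms of the co-primary model one by one without that variable. The label therefore has no described use.

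Two things are at stake, both modest. The first is precision: a baseline variable that predicts the 6-month change would narrow the posterior for the arm difference, and the design is powered at 81%. The second concerns the analysis set. On the article's own reasoning haemoglobin may influence adherence, and so who enters the per-protocol set, as well as the outcome. Randomisation does not guarantee balance once men are selected on adherence, especially when one arm attends supervised classes and the other is coached remotely.

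An undefined label also leaves room to defend either an adjusted or an unadjusted posterior after the data are seen, against a fixed 97.5% threshold.

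**Working it through.** **1. The stated power.** Sample size calculation gives 81% with 100 per arm. It cannot be reproduced, because the margin, SD and dropout are left to Additional file 4, which is not shown. It can be back-solved. Assume a true difference of 0, no dropout, and treat the 97.5% posterior threshold under non-informative priors as a one-sided 0.025 test:

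margin/SD = (1.960 + 0.878) × √(2/100) = 2.838 × 0.1414 = 0.401.

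With an assumed 15% dropout (85 per arm) the ratio is 0.435. The power figures in step 2 are the same either way.

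**2. Effect of adding baseline haemoglobin.** Let r be the partial correlation of baseline haemoglobin with the 6-month change, given baseline score and strata. No document gives it, so the range is an assumption. The residual SD is multiplied by √(1 − r²), hence

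power = Φ(2.838/√(1 − r²) − 1.960), and equivalent sample size = 200/(1 − r²).

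| Assumed r | Reduction in SE | Power | Equivalent n |
|---|---|---|---|
| 0 | 0 | 81.0% | 200 |
| 0.05 | 0.1% | 81.1% | 200.5 |
| 0.1 | 0.5% | 81.4% | 202 |
| 0.2 | 2.0% | 82.6% | 208 |
| 0.3 | 4.6% | 84.5% | 220 |

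A gain of 2 points needs r of about 0.23. The extra degree of freedom costs about 0.2 points (SD inflated by √(194/193)), so at r = 0.05 the change is roughly neutral (80.9% against 81.0%).

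**3. Which part of the range is plausible.** The baseline score is already in the model. Suppose haemoglobin correlates 0.3 with both the baseline and the 6-month score, and the pre-post correlation is b (all assumed):

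r = (0.3 − 0.3b)/√((1 − b²)(1 − 0.09)).

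This gives 0.18 for b = 0.5 and 0.13 for b = 0.7, or about 82% power. Prior ADT duration, also in the model, may absorb some more. The lower half of the table is therefore the better guide.

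**4. Imbalance.** With 100 randomised per arm, the arm difference in baseline haemoglobin exceeds 1.96 × √(2/100) = 0.277 SD, in one direction or the other, in about 1 trial in 20. Left unadjusted, a difference of that size moves the estimate by r × 0.277 = 0.028, 0.055 or 0.083 residual SD for r = 0.1, 0.2 or 0.3. Against the back-solved margin of 0.401 SD, that is about 7%, 14% or 21% of the margin. These figures are for randomisation alone. Selection into the per-protocol set could add to them, by an amount the documents do not allow one to compute.

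**The case against.** The strongest reply is that nothing is wrong. The article never says that haemoglobin belongs in the co-primary model. The tag may be only a role label, and the stated rationale is a decline over time, which suits an explanatory analysis at least as well as baseline adjustment. A fuller covariate list may sit in the full protocol or analysis plan. HbA1c carries the same tag, and nobody would put it in the FACT-F model on that ground alone.

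Much of this stands. The article is not shown to contradict itself on the primary model, and where the tag applies is a matter of clarification. What remains is that the co-primary terms are listed one by one, that list omits a variable the article itself links to both outcomes, and adding it is a concrete change rather than a request for detail. The HbA1c comparison does not undo this: the article's reason for HbA1c concerns exercise and diabetic control, not fatigue or fitness.

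Four stronger readings are tempting, and the documents do not support them:

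- That haemoglobin is collected and never used. It is listed among the biological outcomes, which the Secondary outcomes section analyses by mixed models, and mediation and moderation analyses are left open.
- That the trial has already paid for this precision. The baseline test is standard of care. The only haemoglobin test outside standard care is at 6 months, after randomisation, and should not be adjusted for.
- That power is materially compromised. No correlation is given, and the likely gain is small.
- That chance imbalance biases the comparison. Under randomisation it does not; it is part of the uncertainty that the posterior already expresses. The argument has more force only for the per-protocol set.

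**Conclusion.** The point holds as a minor one. The co-primary ANCOVA, with the baseline score and both stratification factors, is a valid analysis. Adding baseline haemoglobin would improve it slightly: about 0.4 to 1.6 points of power for an assumed partial correlation of 0.1 to 0.2, and 3.5 points at 0.3, before a cost of about 0.2 points for the degree of freedom. These figures rest on an assumed correlation and on a margin-to-SD ratio back-solved from the stated 81%.

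The better argument is the per-protocol primary analysis. The article itself ties haemoglobin to adherence and to outcome, so adjusting for its baseline value removes one possible route of imbalance after selection. It does not remove other selection effects.

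**What to change.** - Add baseline (T0) haemoglobin as a continuous covariate to both co-primary ANCOVAs, and fix this before outcome data are analysed.
- State that the 6- and 12-month haemoglobin values are not adjusted for in the arm comparison, since they follow randomisation and could be affected by the intervention.
- Fill any missing T0 values by simple imputation from baseline data, so that no participant is dropped. The documents do not say how many values may be missing.
- Reconcile the covariate labels for haemoglobin and HbA1c in Table 1 with the Statistical analysis section: say in which model, and at which time point, each acts as a covariate, or remove the label.

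The cost is one model term, one degree of freedom, a short imputation rule and a clarifying sentence. No new data, visits or participants are needed.
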